204 supervision, and practical test scores). Patient interviews including medical history,  
205 the EuroQol 5D (EQ5D) and the Inguinal Pain Questionnaire (IPQ) will be done  
206 preoperatively, at follow up two weeks and one year after surgery. Physical  
207 examination will be undertaken preoperatively in conjunction with the interviews to  
208 verify that the patients meet the inclusion criteria, and also at two weeks and one year  
209 postoperatively in order to detect post operative complications and recurrences.  
210 Expenses associated with the training and the surgeries will be recorded.

211 ***Data analysis:*** Surgical trainee data will be analysed descriptively. Primary endpoints  
212 for patient data include hernia recurrence. Secondary endpoints include postoperative  
213 complications, chronic pain and patient satisfaction. The outcomes following surgery  
214 performed by medical doctors and CHOs will be compared. Results from Sierra  
215 Leone will be compared with results from the other collaborating centres. When  
216 comparing data, two sample t-tests will be used for continuous variables and  
217 Pearson's Chi-square or Fisher exact test will be used for counts. A p-value < 0.05  
218 will be considered statistically significant.

219 Cost effectiveness will be expressed as USD per Disability Adjusted Life Year  
220 (DALY) averted and USD per Quality Adjusted Life Year (QALY) gained. The  
221 EuroQol questionnaire will be used to calculate QALYs gained (before surgery  
222 compared to one year postoperatively).(39) The Inguinal Pain Questionnaire results  
223 will be used to calculate DALYs gained (before surgery compared to one year  
224 postoperatively).(40)

225 The cost analysis will be done from the care provider's perspective. It will include  
226 staff time, material consumption in relation to the surgery as well as hospital overhead  
227 costs and capital costs.

228 Disability weights for the DALY calculation will be achieved by converting the  
229 results from the seven-level IPQ into the three-level disability weights for  
230 abdominopelvic as outlined in the Global Burden of Disease study 2010.(41) The  
231 disability weight one year after the surgery will be subtracted from the disability  
232 weight before the surgery. DALYs averted will be calculated by multiplying the  
233 disability weight difference with the remaining life expectancy of the patient

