according to the WHO life table for Sierra Leone.(42) The mean DALYs averted will be presented.

QALYs gained will be calculated by translating the results from the EQ5D questionnaires into index values. The difference in the index value before and one year after the surgery will be multiplied with the remaining life expectancy of the patient. The mean QALYs gained will be presented.

In line with the Global Burden of Disease study 2010, no time and age weighting will be used.(41) A sensitivity analysis will be undertaken to assess the robustness of the assumptions.

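### The recorded costs are those of the training and the surgeries, while effects are read at one year and extended for life, so later complication care or re-operation can improve the effect without a recorded cost

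*Protocol*

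**What the plan says.** Aim 3 (section 3) is a cost-effectiveness analysis. All details are in section 4.1, Method.

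- **Cost data.** Under Data collection: "Expenses associated with the training and the surgeries will be recorded". No other cost data are mentioned.
- **Cost items.** Under Data analysis: "The cost analysis will be done from the care provider's perspective. It will include" "staff time, material consumption in relation to the surgery as well as hospital overhead" and capital costs. Care after the operation is not named.
- **Outcome.** "Cost effectiveness will be expressed as USD per Disability Adjusted Life Year" averted, and as USD per QALY gained.
- **Effect, DALY.** The weight at one year is subtracted from the weight before surgery. DALYs averted are this "disability weight difference with the remaining life expectancy of the patient".
- **Effect, QALY.** The difference in the EQ5D index before and "one year after the surgery will be multiplied with the remaining life expectancy of the patient".
- **Follow-up.** Physical examination takes place at two weeks and one year "postoperatively in order to detect post operative complications and recurrences". Recurrence is a primary endpoint and complications are a secondary endpoint.
- **Sensitivity analysis.** One is planned, without stated content.

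Section 5 adds that patients will be encouraged to contact the research team about complications during follow-up.

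**The concern.** The two halves of the ratio cover different periods. The recorded costs are tied to the training and the operation. The effect depends on the patient's state a year later, and that state is then carried over the rest of life. A patient who has a wound problem treated in month two, or a recurrence re-repaired in month six, may score well at one year. The recovered health is credited for life, and nothing in the recording plan captures what the provider spent to achieve it. Under a provider perspective that spending is a relevant cost.

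The ratios are meant to influence national policy (section 4.3), and the question is how mesh repair performs when doctors and community health officers deliver it at first-level hospitals. The cost of dealing with complications is part of that answer. A later analysis plan can define the costing formula, but it cannot recover readmission days or procedures that nobody wrote down.

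**Working it through.** **Is there a figure to reproduce?** The protocol gives no cost-effectiveness figure, provider unit cost, complication rate or complication cost. The one usable input is the expected success rate of 98% in the sample-size paragraph. That calculation reproduces with a one-sided 5% level: (1.645 + 0.842)² × 2 × 0.98 × 0.02 / 0.05² = 96.9, or 97 per group as stated. It has no bearing on the costing beyond supplying the 98%.

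**Which events fall in the gap?** Set the cost window against the effect window:

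1. Care given after the operation and before the one-year visit: its benefit is in the one-year score, but no cost is recorded. This is the mismatch.
2. A recurrence first found at the one-year visit: it is not yet repaired, so any loss in EQ5D or Inguinal Pain Questionnaire (IPQ) score is already in the effect and is multiplied over remaining life. Adding the cost of its later repair without crediting the later gain would create the opposite mismatch.
3. Events after one year: neither their costs nor their health effects are modelled.

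Only the first group belongs in the main ratio.

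**Size of the re-repair term.** With the index operation as the cost unit:

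relative addition to mean cost = r × (re-repair cost / index cost) + c × (complication cost / index cost)

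where r is the share of patients re-repaired before one year and c the share treated for a complication.

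- Read 98% success as r = 0.02, re-repair all of these before one year at index cost, and set c = 0. The addition is 0.02 × 1 = 2%. With effects held fixed, both ratios rise by 2%; put the other way, the index-only cost is 0.02 / 1.02 = 1.96% below the full cost.
- The introduction (Financial burden) puts the cost of a hernia repair at USD 50 to 75. This appears in the context of what patients pay and is not a provider cost. As an illustration only, 2% of it is USD 1.00 to 1.50 per patient.
- The 2% is an upper bound for this term under that reading, because recurrences found only at one year do not count.

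**Complication term.** There is no document-based value for c or its cost. Under pure assumption, 10% of patients at 10% of index cost would add 0.10 × 0.10 = 1%, and 30% at 50% would add 0.30 × 0.50 = 15%. The width of that range shows that the term cannot be sized from the protocol.

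**Is anything omitted in the other direction?** The before-after effect implies an untreated hernia as comparator. Emergency surgery for strangulation, which the introduction associates with higher cost, would then be averted, and it is not in the cost list either. A rough scale from the introduction's own figures uses 30 strangulated hernias per 100,000 people per year and a prevalence of 7 to 12%:

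- 0.0003 / 0.12 = 0.25% per hernia per year, and 0.0003 / 0.07 = 0.43%.
- Over an assumed 20 to 40 years: from 1 − (1 − 0.0025)^20 = 4.9% to 1 − (1 − 0.0043)^40 = 15.8%.

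This applies an East African population rate to a prevalence range for Sierra Leone, so it is crude. It does show that an omitted saving could be as large as, or larger than, the 2% re-repair term.

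**The case against.** The strongest reply is that silence is not exclusion. The cost list is introduced as what the analysis will include, which is not exhaustive. The surgeries whose expenses are recorded could be read to cover a re-operation, and the qualifier about the surgery may attach only to materials. Item-level costing is often left to an analysis plan. This stands to a degree: a reader might infer that complications and re-repairs are costed at zero, and the protocol does not say so. What it does say is which expenses are recorded, and that sentence has the same boundary as the cost list. The gap is in collection, where a later plan cannot help.

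A reader might also infer that the reported ratio is too low overall. The document does not support that, because averted emergency surgery is unlisted too and leaving it out pushes the ratio up. The planned effect formula has no explicit term for averted strangulation, so that saving fits a scenario better than the main ratio. Still, the net direction remains open.

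Nor would poor outcomes leave the result untouched. A complication or recurrence that still affects the patient at one year lowers the effect, and does so for life. Finally, 98% success is not defined as freedom from recurrence, so even the 2% rests on an interpretation.

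**Conclusion.** The concern holds as a mismatch between the cost window and the effect window. Followed as written, provider care for complications or re-operation between surgery and the one-year visit can improve the one-year score without a recorded cost. That omission, taken alone, makes the cost per DALY averted and per QALY gained too favourable.

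The demonstrable size is small. Re-repair contributes at most about 2%, assuming that all failures are recurrences and all are re-repaired at index cost before one year. The complication part is unknown. No claim about the net direction of bias across all omitted costs is justified. The point deserves action because collection at the time is cheap and later recovery is difficult.

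**What to change.** 1. **Data collection.** At the two-week and one-year interviews, record groin-related provider care since surgery: unscheduled visits, readmission days, procedures, medication courses and re-operation.
2. **Cost paragraph.** State the cost horizon: the provider cost of this care up to the one-year visit is added to the index cost, using the same unit costs. Do not add to the main ratio the later repair of a recurrence first found at the one-year visit.
3. **Sensitivity analysis already planned.** Show the index-operation-only ratio, together with scenarios for later re-repair and for averted emergency surgery, so that omitted costs and omitted savings are treated alike.

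The cost is a few items at two interviews that already take place and a sentence or two in the protocol. The drawbacks are some recall error, mainly over the interval up to one year, and a slightly less favourable main ratio.

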### ***Equipment and Personnel***

The study requires functioning operation theatres and surgical equipment. To ensure that high volumes of surgery can be performed, we will provide the needed surgical instruments, medicines and materials not available at the selected study sites. Depending on availability, we might need to invest in one reliable autoclave per participating hospital.

The principal investigator based in Sierra Leone will be responsible for co-ordination of all activities of the study, supported by a core team. The principal investigator together with CapaCare will organise training and ensure that additional capacity needs at the chosen hospitals are feasible for the hernia surgery. The core team will be responsible for data collection from recruitment of patients to follow up.

## **4.2. Organization and collaboration**

This project based in Sierra Leone contributes to the multicentre project on Inguinal hernia repair in sub-Saharan Africa. It is part of a collaboration built up of four bilateral partnerships (Sierra Leone-Norway, Uganda-Sweden, US-Ghana/Tanzania).

### **4.3. Plan for implementation**

The results from the study will be used to influence national policy both on hernia repair and on the training of CHOs and non-specialist medical doctors in Sierra Leone.

The results of the study may be presented at national, regional and international level.

- Global: Bi-annual meeting of the World Health Organization's Global Initiative for Essential and Emergency Surgical Care and Alliance for Surgery and Anaesthesia Presence (ASAP)
- Africa: West African College of Surgeons annual conference
- Sierra Leone: Annual biomedical conference in Sierra Leone
- Norway: NTNU Annual Global Health Day
- UK: Royal College of Surgeons, Association of Surgeons of Great Britain and Ireland Annual Conference

## **5. Ethics**

Ethical approval will be obtained from the medical ethics committee in Sierra Leone and Norway. Patients will be included in the study after giving informed consent, information will be provided verbally and in a written form in local languages. The surgeries will be offered free of charge, and transportation costs will be compensated. Participants will be encouraged to contact the research team in case of any complications or questions during the follow up period.

327  
328  
329  
330  
331  
332  
333  
334  
335  
336  
337  
338  
339  
340  
341  
342  
343  
344  
345  
346  
347  
348  
349  
350  
351  
352  
353  
354  
355  
356  
357  
358  
359  
360  
361  
362  
363  
364  
365  
366  
367  
368  
369  
370  
371  
372  
373  
374  
375  
376  
377  
378  
379

